6.3 Safety Monitoring

### **7.0 Statistical Analysis**

|    |                                       |
|----|---------------------------------------|
| 33 | 7.1 Sample Size Calculation           |
| 34 | 7.2 Data Analysis                     |
| 35 | 8.0 Discussion                 |
| 36 | 8.1 Clinical Significance             |
| 37 | 8.2 Anticipated Outcomes              |
| 38 | 8.3 Limitations and Future Directions |
| 39 | 9.0 Data management            |
| 40 | 10.0 Study schedule            |
| 41 | 11.0 References                |

42  
43  
44  
45  
46  
47  
48  
49  
50  
51  
52  
53  
54  
55  
56  
57  
58  
59  
60  
61  
62  
63  
64  
65

66 **1.0 Introduction**

67

68 1.1 Rationale

69 Interstitial Cystitis/Bladder Pain Syndrome (IC/BPS) is a chronic and debilitating condition characterized by  
70 urinary symptoms, including increased urinary frequency, urgency, and pelvic discomfort or pain, often  
71 exacerbated during bladder filling. It affects millions of individuals worldwide and severely impacts their  
72 quality of life. IC/BPS predominantly affects females, with a prevalence ranging from 2% to 17.3% (1),  
73 making it a significant public health concern. Despite extensive research, the precise pathogenesis and  
74 underlying mechanisms of IC/BPS remain elusive, leading to challenges in both diagnosis and treatment.

75

76 Current therapeutic options are limited and often provide only short-term relief. In cases where other  
77 treatment modalities fail, patients may resort to invasive surgeries, with a 23% risk of surgical interventions  
78 failing to improve their symptoms (2). Thus, there is an urgent need to deepen our understanding of the  
79 molecular mechanisms underlying IC/BPS to provide more effective treatments and improve patient care.

80

81 1.2 Study Objectives

82

83 The primary objective of this study is to assess the efficacy and safety of intravesical interferon instillation  
84 as a novel therapeutic approach for women with IC/BPS compared to hyaluronic acid. We aim to determine  
85 whether intravesical interferon offers a more effective and long-lasting treatment option for IC/BPS, and  
86 whether it can improve the quality of life of affected individuals.

87

88 **2.0 Study Background**

89

90 2.1 IC/BPS Prevalence and Impact

91

92 IC/BPS imposes a significant burden on patients' daily lives, affecting their emotional, social, and physical  
93 well-being. The increased frequency and urgency of urination, along with pain, create constant discomfort  
94 and psychological stress. Patients often report difficulty in maintaining employment, social interactions, and  
95 sexual relationships due to the condition. This underscores the importance of finding more effective  
96 treatments to alleviate symptoms and improve the quality of life of those affected.

97

98 2.2 Current Treatment Challenges

99  
100  
101  
102  
103  
104  
105  
106  
107  
108  
109  
110  
111  
112  
113  
114  
115  
116  
117  
118  
119  
120  
121  
122  
123  
124  
125  
126  
127  
128  
129  
130  
131

While a variety of treatment approaches exist, such as oral medications, bladder instillations, and physical therapy, the efficacy of these treatments varies among individuals. Intravesical hyaluronic acid (HA) instillation is considered a third-line treatment option for IC/BPS and is used to improve the defective bladder glycosaminoglycan layer. However, the effectiveness of HA therapy is still uncertain, and many patients experience relapses after discontinuation (3-5). Additionally, there is a lack of long-term follow-up data on the outcomes of HA therapy.

2.3 Viral Involvement in IC/BPS

Recent research has suggested a possible viral etiology in the development of IC/BPS. Some studies have detected a remarkably high positivity rate of BK polyoma virus (BKPyV) and JCPyV in the urine of IC/BPS patients using single-cell sequencing (6-8). Furthermore, it has been reported that intravesical cidofovir treatment was effective in decreasing viral loads of JCPyV and BKPyV, resulting in symptom reduction.

2.4 The Role of Interferon

Interferon, a group of signaling proteins, plays a crucial role in the innate immune system and is known for its antiviral properties (9, 10). Previous research has suggested that interferon can negatively regulate JCPyV and BKPyV infections. This raises the possibility of interferon being a potential specific drug for the treatment of IC/BPS. The current study is the first to explore the efficacy and safety of interferon intravesical instillation for women with IC/BPS compared to HA.

2.5 Hypothesis

It is hypothesized that intravesical interferon instillation will lead to a significant reduction in pain, as measured by the Visual Analog Scale (VAS) score, and will improve IC/BPS symptoms and patient-reported outcomes compared to hyaluronic acid. The study will aim to test this hypothesis rigorously.

3.0 Study Design

3.1 Trial Design

This study employs a double-masked, randomized, phase II/III clinical trial with a parallel group design. A randomized trial design will help ensure the comparability of the two treatment groups, reducing the potential for selection bias.

### 3.2 Study Period

The study will be conducted over the course of October 2022 to April 2023. Data analysis and interpretation are anticipated to occur between October and November 2023.

### 3.3 Ethics and Registration

This study protocol has undergone a rigorous review process and received approval from the Ethics Committee on Biomedical Research (Ethics Committee on Biomedical Research, West China Hospital of Sichuan University, No.2022370). The trial is also registered on ClinicalTrials.gov with the identifier (NCT05912946).

## 4.0 Study Participants

### 4.1 Inclusion Criteria

- 1) Women aged 18–70 years.
- 2) Diagnosis of IC/BPS, confirmed in the absence of active infection or tumor, following the guidelines provided by the Canadian Urological Association (CUA) and the American Urological Association (AUA) (3, 4).
- 3) Symptom duration exceeding six months.
- 4) O’Leary-Sant Interstitial Cystitis Symptom Index (ICSI) and O’Leary-Sant Interstitial Cystitis Problem Index (ICPI) score of 18 or higher.
- 5) Willingness to undergo bladder perfusion therapy and actively participate in follow-up assessments.

### 4.2 Exclusion Criteria

- 1) History of allergy to interferon or hyaluronic acid.
- 2) Serious heart, lung, liver, kidney, or blood diseases.

- 3) Pregnancy or lactation.
- 4) Urinary tract infection within the last two months.
- 5) History of hepatitis B, hepatitis C, or human immunodeficiency disease.
- 6) Recent history of bladder hydrodistension, transurethral resection of the bladder, or sacral neuromodulation within the last three months.
- 7) Treatment with oral medications or intravesical instillation within the last three months.

## **5.0 Randomization and Interventions**

### **5.1 Randomization**

Randomization of patients will be achieved through computer-generated numbers in a 1:1 ratio, with a predefined sequence. A random assignment number will be allocated to each patient and provided to investigators via telephone to maintain blinding.

Blinding was maintained by a numbering system and the use of an investigator to prepare the study medication who did not meet the patients before or after treatment.

### **5.2 Treatment Groups**

1) Interferon Group: Patients will receive intravesical instillation of 1 mL Recombinant human interferon alpha-2b injection (300 international units) mixed with 40 mL sterile saline.

2) Hyaluronic Acid (HA) Group: Patients will receive intravesical instillation of 40 mg/50 mL HA solution.

Both groups will undergo weekly instillations for four weeks, followed by monthly interferon instillations for the subsequent four months. Patients will be instructed to avoid urinating for at least 30 minutes after each instillation to enhance bladder retention.

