## 8.0 Discussion

### 8.1 Clinical Significance

This study aims to address the pressing need for effective treatment options for IC/BPS, a debilitating condition affecting millions of people, predominantly women. By exploring the efficacy of intravesical interferon instillation compared to the current treatment standard, hyaluronic acid, the study seeks to offer a novel therapeutic approach with the potential to alleviate the pain and discomfort associated with IC/BPS and improve the quality of life for affected individuals.

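### Section 5.2 gives monthly interferon to both groups, contradicting its own hyaluronic acid arm and the interferon-versus-HA comparison

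*Protocol*

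**What the plan says.** Section 5.2 defines two arms by agent. The interferon group receives interferon alpha-2b, 1 mL in 40 mL saline. For the HA group it says: "Patients will receive intravesical instillation of 40 mg/50 mL HA solution". Neither definition is limited to a phase of treatment.

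The schedule follows in the same section: "Both groups will undergo weekly instillations for four weeks, followed by monthly interferon instillations for the subsequent four months". This is the only dosing schedule in the text available.

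Elsewhere the trial is described as interferon against HA:

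- Section 3.1: "double-masked, randomized, phase II/III clinical trial with a parallel group design".
- Section 1.2, on the purpose of interferon: "as a novel therapeutic approach for women with IC/BPS compared to hyaluronic acid".
- Section 2.4: "efficacy and safety of interferon intravesical instillation for women with IC/BPS compared to HA".
- Section 2.5, the hypothesis: "will improve IC/BPS symptoms and patient-reported outcomes compared to hyaluronic acid".
- Section 8.1: "interferon instillation compared to the current treatment standard, hyaluronic acid".

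None of these mentions a switch, a crossover or a common maintenance phase.

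**The concern.** The schedule sentence has both groups as its subject and names interferon as the monthly agent. Followed as written, it moves the control arm onto the experimental drug once the four weekly instillations are done. The trial would then compare two induction agents, each followed by interferon maintenance. That is a different trial from the one in the objectives and hypothesis.

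Three parts of the protocol would carry the change into the results:

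- Section 6.1 gives no time point for the change in pain score, and section 7.2 plans a repeated-measures analysis of all available data at each time point. Nothing in the text limits the comparison to the first four weeks.
- Section 1.2 asks whether interferon is longer lasting as well as more effective, a question that depends on the later period.
- Section 6.3 collects adverse events until one month after the last instillation, so events on interferon would be counted in the HA group.

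Which drug the control arm receives is a protocol matter and would not normally be left to a statistical analysis plan.

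**Working it through.** **Does the text conflict?**

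| Place in protocol | Agent for HA group, weekly phase | Agent for HA group, monthly phase |
|---|---|---|
| 5.2, arm definition | HA | HA (no phase limit stated) |
| 5.2, schedule sentence | not named | interferon |
| 1.2, 2.4, 2.5, 8.1 | HA as comparator | HA as comparator; no switch mentioned |

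The monthly-phase entries cannot all be right. HA followed by interferon is a possible regimen, but no section shown describes it.

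**How much treatment is affected?**

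Inputs: four weekly instillations and four months of monthly instillations (section 5.2); 17 patients per group and a minimum of 13 before dropout (section 7.1). Assumption: one instillation per month.

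The planned group size reproduces: 13 / (1 − 0.20) = 16.25, rounded up to 17.

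- Instillations per patient: 4 + 4 = 8.
- Monthly share: 4 / 8 = 50%.
- HA group, all 17 completing: 17 × 8 = 136 instillations, of which 17 × 4 = 68 would be interferon.
- For 13 patients with complete treatment: 13 × 8 = 104, of which 13 × 4 = 52 would be interferon. This is not a group total, because it leaves out instillations given to patients who drop out.

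If the sentence is a slip and each arm keeps its agent, the affected count is 0.

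**What cannot be calculated?** Section 7.1 states no effect size or standard deviation, and nothing in the protocol says how much of a treatment difference would remain once both arms receive interferon. Any figure for lost power or a diluted pain contrast would rest on an invented fraction, so none is given.

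**The case against.** The strongest reply is that this is an obvious slip. The arm definitions and every statement of the comparison point to each group keeping its own drug, and in that case nothing is harmed. That is probably right about intent, but it does not correct the sentence. The wrong agent for the control arm stands in the treatment section, and no other text shown overrides it.

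Other points on that side:

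- *Parallel groups.* Patients randomized to interferon throughout or to HA then interferon would still form parallel groups. This stands. The firm conflict is with the HA arm definition and the stated comparison; section 3.1 adds only that no switch is described.
- *Masking.* One could argue that an error would go unnoticed because section 5.1 provides for "the use of an investigator to prepare the study medication who did not meet the patients before or after treatment". That is weak support. The interferon instillation is about 41 mL (1 + 40) and the HA instillation 50 mL, so staff might notice a change. Section 5.1 also does not say what instructions the preparer follows. The finding does not need this argument.
- *Timing of the primary comparison.* With no time point in section 6.1, the main contrast might fall before the monthly phase, and an analysis plan not shown could fix this. That limits what can be said about the primary result. The durability question and the adverse-event data would still be affected if the sentence were followed.
- *Missing schedule.* Section 10.0 is listed in the contents but is not in the text available, and it might name the agent at each visit. A correct schedule would reduce the practical risk but leave section 5.2 contradicting it.

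**Conclusion.** The concern holds. Section 5.2 assigns interferon to both groups for the monthly phase, against its own HA arm and the comparison the trial is meant to make. The consequence depends on what is done: none if each arm keeps its agent, or half of each HA patient's instillations (4 of 8; 68 of 136 for the planned group) if the sentence is followed. Those counts assume one instillation per month and, for the group total, that all 17 patients complete treatment. In the second case the stated contrast is lost after week 4. It must be fixed because the two readings describe different trials.

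**What to change.** Reword the schedule sentence so that, after the four weekly instillations, each group continues once a month for four months with the agent to which it was assigned. Bring the medication preparation instructions and the study schedule into line. This is the only reading consistent with the rest of the protocol, but the sponsor should confirm it.

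If a switch to interferon in the HA group was intended, the protocol should say so and justify it, set the primary assessment before the first monthly instillation, and restate the durability and safety comparisons accordingly.

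The first option costs a one-sentence amendment and matching instructions. It adds no patients, visits or procedures, and the 13 and 17 per group in section 7.1 are unchanged.

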## **6.0 Main Outcomes and Measures**

### **6.1 Primary Endpoint**

The primary endpoint of this study is the change in the Visual Analog Scale (VAS) score for pain intensity.

198 The VAS score measures pain intensity on a numerical rating scale ranging from 0 (indicating no pain) to 10  
199 (indicating the worst pain ever). Clinical importance will be defined as a reduction in pain of approximately  
200 30% from baseline.

## 202 6.2 Secondary Endpoints

204 1) 24-hour voiding frequency.

205 Functional bladder capacity (maximum voiding volume on a 3-day voiding diary).

206 2) Nocturia episodes.

207 3) Interstitial Cystitis Symptom Index (ICSI) score.

208 The O’Leary-Sant instrument is comprised of Symptom Index (score range: 0-20 points), which contains  
209 four questions related to urinary and pain symptoms. The score is calculated by summing the points for each  
210 item, and a score  $\geq 6$  points indicates IC.

211 4) Interstitial Cystitis Problem Index (ICPI) score.

212 The O’Leary-Sant instrument is comprised of Problem Index (score range: 0-16 points), which contains four  
213 questions related to urinary and pain symptoms. The score is calculated by summing the points for each item,  
214 and a score  $\geq 6$  points indicates IC.

215 5) A symmetric seven-point Global Response Assessment (GRA) scale

216 GRA scores categorized into 7, 6, 5, 4, 3, 2, and 1, indicating markedly worse to markedly improved status.

217 GRA responder is defined as at least a two-point change in GRA.

## 219 6.3 Safety Monitoring

221 Adverse events will be closely monitored from the time of the first infusion through one month after the last  
222 instillation, including urinary tract infection, bladder irritation, urinary flow problems, psychiatric symptoms,  
223 fever, liver function abnormalities, kidney function abnormalities, and gastrointestinal symptoms. Routine  
224 urine analysis, blood chemistry, and blood routine will be conducted at patient visits.

## 226 7.0 Statistical Analysis

### 228 7.1 Sample Size Calculation

230 To achieve 90% power with a 2.5% significance level, we have determined that a minimum of 13 patients is

required in each group. Factoring in a 20% dropout rate, the final sample size is set at 17 for each group.

## 7.2 Data Analysis

All analyses will be performed on an intention-to-treat basis, including all available participant data at each time point, regardless of treatment adherence. Clinical data with continuous variables will be presented as the mean  $\pm$  standard deviation, while categorical variables will be presented as percentages. Proportions will be compared using the  $\chi^2$  test.

Primary and secondary outcome measurements will be analyzed using repeated measures analysis to examine differences between time-based measurements. Statistical significance will be considered when  $p < 0.05$ . Data analysis will be performed using SPSS version 24.0 for Windows (SPSS Inc., Chicago, IL, USA).

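### Section 7.2 applies intention-to-treat to every analysis with no exception for safety, so any woman given the other drug, or never instilled, could blur the adverse-event comparison

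*Protocol*

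**What the plan says.** Section 7.2 sets one basis for the whole analysis: "All analyses will be performed on an intention-to-treat basis, including all available participant data at each time point, regardless of treatment adherence". It makes no exception for safety, and no safety or as-treated set is defined elsewhere in the protocol. The same paragraph says that categorical variables are shown as percentages and adds "Proportions will be compared using the" chi-squared test, which is the natural route for adverse-event rates. Primary and secondary outcomes come in a separate paragraph.

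Two other sections bear on this:

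- Section 1.2 puts safety in the main objective: the "primary objective of this study is to assess the efficacy and safety of intravesical interferon instillation" against hyaluronic acid (HA).
- Section 6.3 opens the observation window at treatment, not at randomisation: "Adverse events will be closely monitored from the time of the first infusion through one month after the last" instillation.

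**The concern.** Intention-to-treat suits efficacy, where dilution of a difference is usually the cautious error. For harms, dilution works the other way, because a real excess on one drug looks smaller than it is. Two kinds of women matter.

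- **Given the other drug.** Her adverse events are counted against the arm she was randomised to, not the drug that she received.
- **Never instilled.** Under section 6.3 she has no observation window. If she still counts in the denominator as event-free, her arm's rate is too low.

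Section 2.4 presents this as the first study of intravesical interferon against HA in these women, so a clear account of harms by drug matters. The arms are small, and a few women can shift the rates.

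**Working it through.** **Inputs from the protocol.** Allocation is 1:1 (section 5.1). Section 7.1 says: "To achieve 90% power with a 2.5% significance level, we have determined that a minimum of 13 patients is" required per group, and then "Factoring in a 20% dropout rate, the final sample size is set at 17 for each group".

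**The plan's own figure.** 13 / (1 − 0.20) = 16.25, rounded up to 17 per arm. This reproduces.

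**Inputs that are assumptions.** The protocol gives no adverse-event rates, no number never instilled and no number given the other drug. Let pI and pH be the true rates on interferon and HA. In each arm of 17, let k women be never instilled and counted as event-free, and let x women be given the other drug.

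**Expected rates by randomised arm.**

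- Interferon arm: [(17 − k − x)·pI + x·pH] / 17
- HA arm: [(17 − k − x)·pH + x·pI] / 17
- Difference: (pI − pH)·(17 − k − 2x) / 17

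The share of the true difference that is kept is therefore (17 − k − 2x)/17, whatever the rates:

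| k per arm | x per arm | Share kept | 40% v 10% (true 30 points) | 30% v 10% (true 20 points) |
|---|---|---|---|---|
| 0 | 0 | 100% | 30.0 | 20.0 |
| 1 | 0 | 16/17 = 94% | 28.2 | 18.8 |
| 2 | 0 | 15/17 = 88% | 26.5 | 17.6 |
| 0 | 1 | 15/17 = 88% | 26.5 | 17.6 |
| 0 | 2 | 13/17 = 76% | 22.9 | 15.3 |
| 1 | 1 | 14/17 = 82% | 24.7 | 16.5 |
| 2 | 2 | 11/17 = 65% | 19.4 | 12.9 |

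Rates of 50% v 20% give the same differences as 40% v 10%.

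**Shift per woman, at 40% v 10%.** One never-instilled interferon woman lowers that arm's expected rate by 0.40/17 = 2.4 points, from 40% to 37.6%. One woman given the other drug moves her randomised arm's expected rate by 0.30/17 = 1.8 points.

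**Unequal losses.** If only the interferon arm has two never-instilled women, its rate is 0.40 × 15/17 = 35.3% and the excess is 25.3 points. If only the HA arm has two, its rate is 0.10 × 15/17 = 8.8% and the excess is 40 − 8.8 = 31.2 points, larger than the true 30.

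**Against sampling error.** At 40% v 10% with 17 per arm, the standard error of the difference is √(0.4·0.6/17 + 0.1·0.9/17) = 0.139, or about 14 points.

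**The case against.** The strongest case on the other side has five parts.

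- **The sentence may have been meant for efficacy.** Section 7.2 never mentions adverse events, and safety sets are commonly left to the analysis plan, which is not at hand. This stands only in part. The wording covers every analysis, so a plan that defined a separate safety set would contradict the protocol as written.
- **Never-instilled women may already be left out.** The sentence refers to available data, and section 6.3 starts observation at the first infusion, so a woman never instilled has no adverse-event data. This is a fair reading, and that half of the point is conditional on it. The two readings give different denominators, which should be settled. The other-drug half does not depend on it.
- **Nothing suggests many wrong-drug cases.** Section 5.1 describes a numbering system and an investigator who prepares the medication apart from the patients. One or two such women per arm would be 6% to 12%, and the protocol gives no reason to expect that. This stands.
- **The shifts are small.** In the table with one or two women of a single kind per arm, they run from about 1 to 7 points, well inside a standard error of about 14. This stands as to size. The errors differ in kind, however: wrong-drug assignment is a systematic pull towards no difference, and one that can be avoided.
- **Grouping by drug received may be unclear.** Section 5.2 describes the monthly phase for both groups as interferon. Read literally, HA women would receive both drugs. This stands, and it limits the repair until the section is reconciled.

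A reader might also infer that the rule can only flatter interferon. It cannot be put so strongly: never-instilled women in the HA arm alone raise the apparent excess to 31.2 points, and if HA had the higher event rate, wrong-drug cases would make interferon look worse. Nor does each such woman move a rate by about 6 points. That is 1/17 = 5.9 points, the change when one actual event is added or removed; the expected shifts are 1.8 to 2.4 points at the assumed rates.

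**Conclusion.** The point holds as a minor one. Section 7.2 states a rule that, taken literally, analyses harms by randomised arm. That is the wrong basis for a comparison of harms by drug, in a trial that names safety in its primary objective. Because the rule is written into the protocol, it is a badly fixed rule, not a gap left to the analysis plan.

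Its size depends on events that may not happen. The single-deviation cases keep 94% (k = 1) or 88% (x = 1) of a true risk difference, and the loss is zero if every woman receives at least one instillation and only her allocated drug. The shares assume equal numbers of such women in the two arms, and the never-instilled part also assumes that these women are counted as event-free. The figures in points rest on illustrative event rates. The documents do not show that dilution will occur, and they do not fix its direction for unequal losses.

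**What to change.** In section 7.2, limit the intention-to-treat sentence to the efficacy endpoints and add, for example: *Adverse events and laboratory abnormalities are analysed in all women who received at least one instillation, grouped by the drug actually received, from the first instillation.* This agrees with the window already set in section 6.3 and settles the denominator.

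Before it is applied, section 5.2 must be reconciled: its description of the monthly phase for both groups does not fit the two arm definitions above it, and grouping by drug received has no clear meaning for HA women until it does.

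The cost is one sentence. Safety denominators may fall slightly below 17 per arm. Recruitment and the efficacy analysis are unchanged, and if there are no such deviations the safety results are unchanged too.

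### The stated repeated measures analysis of VAS change names no adjustment for baseline, which costs precision and over-corrects chance imbalance at 13 to 17 women per arm

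*Protocol*

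**What the plan says.** Section 6.1 of the protocol defines the outcome: "The primary endpoint of this study is the change in the Visual Analog Scale (VAS) score for pain intensity". It judges clinical importance by a fall in pain of roughly "30% from baseline". Baseline VAS is therefore needed for every woman in the analysis.

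Section 7.2 names the method for that endpoint and for the secondary outcomes: "Primary and secondary outcome measurements will be analyzed using repeated measures analysis to examine differences between time-based measurements". The analysis is by intention to treat, "including all available participant data at each time point, regardless of treatment adherence". The significance threshold (p below 0.05) and the software are also given. The section states no baseline covariate and does not say whether baseline is one of the repeated measurements or something adjusted for.

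Section 7.1 sets the size: "To achieve 90% power with a 2.5% significance level", 13 women per group are needed, and then "Factoring in a 20% dropout rate, the final sample size is set at 17 for each group".

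**The concern.** There are two usual ways to bring baseline into a comparison of pain over time without a covariate: subtract it from each follow-up value, or treat it as the first time level and test whether the arms differ in their course. With one baseline and one follow-up value, the arm-by-time test of a classical repeated measures analysis is the same test as an unadjusted t-test on the change.

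Both deduct the whole baseline difference between arms, whereas with equal variances only a fraction r of it is expected to persist to follow-up. The arm that starts higher by chance therefore shows a larger fall through regression to the mean, whatever the treatment does. The extra noise also widens the confidence interval. A trial of 34 women has little precision to spare, and chance baseline differences are larger in small arms. Section 5.1 describes no stratification on baseline pain that would limit them. The same reasoning applies to ICSI, ICPI, voiding frequency, nocturia and functional bladder capacity.

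**Working it through.** **Inputs from the protocol.** 13 evaluable and 17 enrolled per group, 20% dropout, 90% power, 2.5% significance level (7.1); p below 0.05 (7.2); endpoint is VAS change (6.1).

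**Assumptions, because the protocol gives no figure.** Baseline and follow-up VAS have equal variance s². Their correlation r is 0.3, 0.5 or 0.7. The 2.5% level is taken as one-sided, which matches a two-sided 5% test.

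**The plan's own figure.** 13/(1 − 0.20) = 16.25, rounded up to 17, which agrees with 7.1. The 13 itself cannot be reproduced, because no effect size or SD is stated. Working backwards, 90% power with 13 per arm implies a standardised effect of 1.27 by the normal approximation, or 1.33 with the t distribution.

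**Variance ratio.**
- Variance of a change score: 2(1 − r)s².
- Residual variance with baseline as a covariate: (1 − r²)s².
- Ratio: (1 − r²)/[2(1 − r)] = (1 + r)/2.
- Estimating the covariate slope inflates the variance by about 1 + 1/(2n − 4). At n = 13 this is 1 + 1/22 = 1.045.

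**Power at 13 per arm, two-sided 5%.** The change-score test has 24 degrees of freedom and noncentrality d√(n/2). The adjusted test has 23 degrees of freedom, with that noncentrality divided by the square root of the cost-adjusted ratio.
- At 90% power on the change score: d = 1.326, noncentrality 1.326 × √6.5 = 3.38.
- At 50% power on the change score: d = 0.801, noncentrality 0.801 × √6.5 = 2.04.

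| r | ratio (1 + r)/2 | ratio after cost | noncentrality from 3.38 | power instead of 90% | noncentrality from 2.04 | power instead of 50% |
|---|---|---|---|---|---|---|
| 0.3 | 0.65 | 0.68 | 4.10 | 97.5% | 2.48 | 66% |
| 0.5 | 0.75 | 0.78 | 3.82 | 95.5% | 2.31 | 60% |
| 0.7 | 0.85 | 0.89 | 3.59 | 93% | 2.17 | 55% |

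The 50% row is an illustration and is not in the protocol. It shows what adjustment is worth if the true effect is smaller than the one that 13 per arm was sized for.

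**Size of chance imbalance.** The baseline difference between arms has standard error √(2/n) in SD units: 0.39 at n = 13 and 0.34 at n = 17. A gap above 0.5 SD arises by chance with probability about 20% and 14% respectively. With equal variances, a gap of 1 VAS point moves the unadjusted change contrast by (1 − r) points: 0.7, 0.5 or 0.3 at the three values of r.

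**The case against.** A reader might infer that the primary analysis ignores baseline VAS altogether and leaves chance imbalance uncorrected. The protocol does not support that. The endpoint is a change and the comparison is between time points, so baseline does enter. The fault is over-correction, and the larger loss that would come from comparing follow-up VAS alone does not arise from this text. Nor is adjustment strictly free: it costs a degree of freedom. Even against follow-up VAS alone, its gain at 13 per arm disappears at r of about 0.2, where (1 − 0.04) × 1.045 = 1.00.

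The strongest objection is that 7.2 gives no model terms at all. Repeated measures analysis is compatible with a model that includes baseline, and a list of covariates is commonly left to a statistical analysis plan, which is not shown here. In a randomised trial the change score is also unbiased over repeated randomisations, so the issue is efficiency and the result in the one sample drawn, not systematic bias.

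Most of this stands, and it lowers confidence. It does not remove the point. Section 7.2 fixes the method and its purpose, and that purpose is comparison of times. Baseline as a time level, change without a covariate, and baseline as a covariate all fit the sentence, and they can give different answers in the same 34 women. The adjusted form is the more precise one at each assumed r, after its cost.

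**Conclusion.** The point holds as a concrete improvement to the stated method. As written, 7.2 points to an analysis in which baseline is subtracted or is one of the time levels. Compared with that, adjustment for baseline would cut the variance of the VAS contrast by about 32%, 22% or 11% at r = 0.3, 0.5 or 0.7 with 13 per arm (1 minus 0.68, 0.78 and 0.89). If the 90% power claim is true for the change score, the gain is about 3 to 7.5 percentage points. If the effect is smaller than planned for, it is about 5 to 16 points.

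These figures rest on equal variances at baseline and follow-up, on a range of r that the protocol does not supply, and on a two-sided 5% test. Confidence is moderate, since an unseen analysis plan may already name the covariate.

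**What to change.** In section 7.2, state that VAS and each continuous secondary outcome are compared between arms with the woman's own baseline value of that outcome as a covariate. Either form will do:
- ANCOVA at the primary time point; or
- a repeated measures model with only the post-baseline visits as outcomes, with baseline and baseline-by-visit terms.

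Report the adjusted between-arm difference with its 95% confidence interval. If an analysis plan already specifies this, bring the sentence in 7.2 into line with it.

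The cost is a sentence or two of text and, for ANCOVA, one degree of freedom. No new data, visits or patients are needed.
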